### 2.3. Research team

The research team will include 4 participants. Two researchers will be responsible for the evaluation of the groups—the control group and experimental group; one researcher responsible for the experimental group instruction; one staff member that is not related to the study to perform the randomization; one researcher will perform the data analysis.

### 2.4. Randomization

After evaluation of the inclusion and exclusion criteria, the participants eligible to participate in the study will be randomly separated into two groups: the control group (CG): which will have no activities performed; the experimental group (EG): which will follow the strength exercises protocol.

The randomization of the participants will be performed by an individual not directly related to the study. To avoid selection bias, random numbers will be generated by computer; the distribution will be made from a website: www.randomization.com. For the statistical analysis, the researcher in charge will receive the data without identifying the participants to obtain the results in a blinded manner. A randomization with a 1:1 computer-generated will be made for the group allocation.

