## 2. Materials and methods

### 2.1. Study design

The present study protocol refers to a single-blind, randomized controlled trial, developed according to Standard Protocol Items: Recommendations for Interventional Trials (SPIRIT) (34). The volunteers will be allocated randomly to the intervention group that will receive the exercise program or the control group. A staff member not involved in the study will be responsible for the randomization based on a computer-generated random number. The intervention program will last 12 weeks, consisting of 8 weeks of strength training plus 4 weeks of no training for the intervention group. The 1-month period will serve to evaluate how long the effects of the training will still be present after the training has ceased. The flow chart of the study design is represented in Figure 1.

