### 2.2. Participants

The project will be publicized to find volunteers for the research. For this action, strategies such as flyers, web advertisements, clinical and health professional referrals, email disclosures, and contact from the fibromyalgia associations database will be used for participant recruitment.

After this initial recruitment, participants of both genders with a medical diagnosis of fibromyalgia according to the American College of Rheumatology criteria aged ≥18 years will be eligible to be included in the study. As exclusion criteria, it would be defined as severe comorbidity or any other type of condition that negatively influences participation in the training program; cognitive disorders; heart problems; surgeries or fractures in the last 6 months; regular practice of physical exercises in the least 3 months before the program. Will be discontinued from the study participants that: 1. change medication or dosage during the program; 2. start a regular practice of physical exercises in parallel to the training program; 3. If the participant request. Before the beginning of the program, the participants will be carefully informed about the research, and informed consent must be given before the beginning of the training program. The present research project was approved by the Ethics Committee of the University of Beira Interior, Portugal (CE-UBI-Pj-2021-017).

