### 2.7. Intervention

#### 2.7.1. Experimental group

To include participants from all over the country, the training program will be carried out through real-time videos. The protocol consists of 8 weeks of training, consisting of 16 sessions of 50 mins, twice a week on alternate days. To facilitate follow-up during practice and reduce the risk of dropout, the volunteers will be divided into two groups with different times for each intervention. All volunteers will perform the exercise protocol at the meeting via an online (Google Meet platform) and both interventions will be performed during the same shift of the day. Each group will consist of 6 to 8 online participants. The sessions will be conducted and supervised by a physical therapist. Volunteers will be instructed about the exercises, protection and how to use the Borg scale at beginning of the meeting. During the meeting, before each exercise, the movement will first be demonstrated by the physical therapist, and then, sets and repetitions will be informed. To ensure that each participant will do the same number of sets and repetitions, all participants will perform the movement during the professional's count. This format will make it easier to count the rest time.

The program will consist of 10 mins of warm-up, 35 mins of strength exercises, and 5 mins of cool-down. The Borg scale will be used to monitor fatigue and perceived effort during practice (43). The protocol of the exercises to be performed during the training program, as well as their progression, are described in Tables 2, 3, respectively.

**Table 2 T2:** Description of strength training.

**Exercise**	**Name**	**Description**	**Position**	**Muscles**
Exercise 1	Sumô Box Squat	Stand near the chair with your feet wider than shoulder width. Start the movement standing with your hips and sit back. Be careful with the chest, knees, and shins.	Stand	**Primary:** Quadriceps. **Secondary:** Gluteus maximus, medius, and minimus; hamstrings, adductor magnus, longus, and brevis; erector spinae.
Exercise 2	T-exercise	From a standing position, bend at the hips and maintain a neutral spine. Perform dynamic motions by forming a T with the arms and return to starting position.	Stand	**Primary:** Lower and middle trapezius; rotator cuff musculature; posterior deltoid. **Secondary:** Hamstrings; gluteus maximus.

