### 2.9. Sample size calculation

The G-power software was used to detect a moderate effect size (partial eta squared of 0.09) in the intra/inter-group comparison. Considering an alpha value of 5%, the total number of participants should be 24 so that the power of the results is 90%. Considering a 20% of dropout risk, a minimum of 30 participants will be recruited (15 for each group).

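### Allocation is not balanced on sex, so the few men may cluster in one arm and make the raw between-group comparisons of jump and throw less precise

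*Protocol article*

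**What the plan says.** Section 2.4 of the protocol article gives the ratio and the tool: "random numbers will be generated by computer; the distribution will be made from a website", and then "A randomization with a 1:1 computer-generated will be made for the group allocation". Section 2.1 adds that a staff member outside the study "will be responsible for the randomization based on a computer-generated random number". Neither section names a factor on which the arms are to be balanced.

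Four other parts of the article bear on this:

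- Section 2.2 admits "participants of both genders with a medical diagnosis of fibromyalgia", and the introduction says that the disease affects mainly women.
- Section 2.9 intends equal arms: "a minimum of 30 participants will be recruited (15 for each group)".
- Section 2.6 and Table 1 score jump height and 2 kg throw distance as raw performance, with no correction for sex. Gender is collected as descriptive data.
- Section 2.10 compares the groups by repeated measures ANOVA, or by a Kruskal-Wallis test if the data are not normal. Sex appears in neither.

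**The concern.** Thirty people with a handful of men is the setting in which unstratified allocation can leave one strong prognostic factor badly split. Men can be expected to jump higher and throw further than women whatever the training does. If two, three or four men land together, the arms differ at baseline on jump and throw, and the raw between-group comparison carries that difference at every visit.

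The comparisons exposed are the group term of the ANOVA and the Kruskal-Wallis fallback, which section 2.10 describes without any baseline adjustment. What is at stake is the precision of these comparisons and how readily a reader will accept the arms as comparable. The concern covers jump and throw only. Nothing in the article suggests a comparable sex effect on the FIQ-P, the symptom scales or balance.

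**Working it through.** **The plan's own figures.** Section 2.9 states: "the total number of participants should be 24 so that the power of the results is 90%". Partial eta squared 0.09 gives f = √(0.09/0.91) = 0.314. With two groups, three measurements, alpha 5%, and an assumed correlation of 0.5 and sphericity, the within-between interaction has 91.4% power at N = 24 and 88.6% at N = 22, so 24 reproduces. With dropout, 24/(1 − 0.20) = 30, or 15 per arm. Fifteen also fits the two online sessions of section 2.7.1 ("Each group will consist of 6 to 8 online participants") as 7 + 8. The arm sizes are therefore consistent, and the check below takes 15/15 as fixed.

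**Chance that all m men share an arm, given 15/15.** The formula is 2·C(30 − m, 15 − m)/C(30, 15).

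- m = 2: 2 × (15·14)/(30·29) = 420/870 = 48.3%
- m = 3: 2 × (15·14·13)/(30·29·28) = 5460/24360 = 22.4%
- m = 4: 2 × (15·14·13·12)/(30·29·28·27) = 65520/657720 = 10.0%

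Fixing the arm sizes hardly helps: with unrestricted allocation the figures are 50%, 25% and 12.5%. Blocking and sex balance are separate matters.

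**Shift in throw when it happens.** The article gives no sex gap and no SD. Assume that men throw 30% to 50% further than women and that the within-sex SD is 18% of the women's mean. The gap is then δ = 0.30/0.18 to 0.50/0.18 = 1.67 to 2.78 SD. A 3–0 split shifts the raw arm difference by 3/15 × δ = 0.33 to 0.56 SD. Doubling the SD to 36% halves this to 0.17 to 0.28 SD.

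**Average cost in precision.** In units of the within-sex variance, the raw arm difference has variance 2/15 = 0.1333 from person-to-person variation. Random placement of m men adds (4δ²/225) × m(30 − m)/116. With balance on sex the addition is 0 for even m and δ²/225 for odd m.

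| Men | δ | Variance, unstratified | Variance, balanced | Reduction in SE |
|---|---|---|---|---|
| 2 | 1.67 | 0.1572 | 0.1333 | 8% |
| 2 | 2.78 | 0.1996 | 0.1333 | 18% |
| 3 | 1.67 | 0.1678 | 0.1457 | 7% |
| 3 | 2.78 | 0.2291 | 0.1676 | 14% |
| 4 | 1.67 | 0.1776 | 0.1333 | 13% |
| 4 | 2.78 | 0.2563 | 0.1333 | 28% |

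The reduction in SE is 1 − √(balanced/unstratified). With the SD at 36% the same formula gives about 2% to 10%.

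**Validity.** I simulated three men, these gaps and no training effect. The Kruskal-Wallis test rejected in about 5% of trials when the men were placed at random. Among trials in which the split was 3–0, it rejected in about 9% to 12%. The error rate is sound over all allocations and poor only after an unlucky one.

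**Interaction.** If sex adds the same constant at each visit, it drops out of each person's change and so out of the group-by-time interaction.

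**The case against.** The strongest case against the point is that randomisation is valid without stratification, so a chance imbalance in sex is not an error. The size of the harm also rests on three figures the article does not give: the number of men, the sex gap and the SD. The sample size reproduces for a within-person effect, on which a constant sex difference has little influence. Kruskal-Wallis is only a fallback. All of this stands, and it is why the point is an improvement and not a defect in validity.

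It can also be said that an article condenses a fuller protocol, which may already stratify. That is possible. If so, one sentence in section 2.4 closes the allocation part.

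Two stronger readings are tempting and are not supported:

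- A reader might infer simple, unrestricted allocation. A 15/15 split would then occur only 14.4% of the time, and the experimental arm would fall outside the 12 to 16 that two sessions hold 39.3% of the time. The article never says that allocation is unrestricted. Section 2.9 intends 15 per group, which fits the sessions, and block details are commonly left to the full protocol. These figures are no evidence of an error.
- A reader might set the 0.33 to 0.56 SD shift against d = 2 × 0.314 = 0.63 and call the two comparable. The planned effect was sized for a repeated-measures comparison, not for a raw difference in level between arms, so they do not measure the same thing.

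**Conclusion.** The point holds as a low-cost improvement. Nothing in the article balances the arms on sex, and no planned between-group comparison takes sex into account. With 15 per arm, all men share an arm with probability 48%, 22% or 10% for two, three or four men.

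The consequence is lost precision and comparability in the raw between-group comparisons of jump and throw. Under the assumed gap and an SD of 18%, balancing on sex reduces the standard error of the arm difference in throw by 7% to 28%; with twice that SD, by 2% to 10%. The jump was not computed separately; the same formula applies with its own gap and SD. There is no bias over repeated randomisation, the group-by-time interaction is largely unaffected, and neither the sample size nor the arm sizes are in dispute.

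**What to change.** In section 2.4, state that the computer-generated list is stratified by sex, with small permuted blocks whose size is not disclosed, held by the independent staff member already named. Blocks need to be small among the men: with blocks of four and two men, both still share an arm in 2 of the 6 possible sequences (1/3), whereas blocks of two keep the arms within one man of each other.

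If all 30 are enrolled before training starts, allocate in one step: split the men at random so that the arms differ by at most one man, then let randomly chosen women fill each arm to 15. This also works when the number of men is odd, where halving each sex separately would not.

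In section 2.10, include sex in the between-group analysis of jump and throw, so that the analysis reflects the stratification.

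The cost is one list setting and a sentence in each of the two sections. Sex is already collected and no staff are added. The downside is slight predictability at the end of a block if allocation is sequential, which the one-step split removes. It must be done before allocation, because it cannot be added afterwards.

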### 2.5. Data collection and procedures

The collection will take place in the facilities of the institutions related to fibromyalgia closest to the participants. If the volunteer cannot attend, the evaluation will be conducted in a public and neutral environment near the region where the research participant lives.

After the training period (8 weeks), the following week the participants of both EG and CG groups will be re-evaluated. From the 9th week on, the beginning of the off-training period will be accounted for, which will last 4 weeks. After this time, there will be a new reevaluation of both groups for future comparison. A schematic diagram of the schedule and steps is shown in Figure 2.

**Figure 2 F2:**
[figure not shown]
Schematic diagram of steps and procedures.

### 2.6. Outcome measures

The tests regarding the evaluation will be performed in one moment. First, demographic, and anthropometric data will be collected, followed by the Fibromyalgia impact questionnaire (FIQ-P), symptoms and balance evaluation. Neuromuscular performance data will be collected at the end so as not to influence the symptoms.

For descriptive data, the following information will be collected: sociodemographic data—age, gender, occupation, region address, marital status, history of falls (35), and due to the actual scenario of COVID-19, if there was contagion and the date of contagion will also be collected. Anthropometric measures such as weight (kg) and height (cm) will be measured using a bioimpedance scale and a stadiometer, respectively. Body mass index (BMI) will be calculated as weight (kg) divided by height (m) squared. All variables and information about the instruments are summarized in Table 1.

**Table 1 T1:** Variables, instruments, interpretation, and reference for assessment.

**Variables**	**Instruments**	**Interpretation of instruments**	**Author and Year**
Functional capacity	FIQ-P	Scores vary from 0 to 100. Higher the value, the greater the impact of fibromyalgia.	Rosado et al. (36)
Pain intensity	VAS	Scores from 0 to 10. Higher the number, the higher intensity.	McCormack et al. (37)
Anxiety level	VAS	Scores from 0 to 10. Higher the number, the higher intensity.	McCormack et al. (37)
Fatigue level	VAS	Scores from 0 to 10. Higher the number, the higher intensity.	McCormack et al. (37)
Mood	VAS	Scores from 0 to 10. Higher the number, better state of mood.	McCormack et al. (37)
Quality of sleep	VAS	Scores from 0 to 10. Higher the number, the worse quality of sleep.	McCormack et al. (37)
Neuromuscular performance	Vertical Jump	Optical measurement system consisting of two transmitting and receiving cells. Higher jump, better neuromuscular performance.	Gonçalves et al. (41)
	Medicine Ball Throw	2kg medicinal ball throw. Higher distance, better neuromuscular performance.	Gonçalves et al. (41)
Balance	Force plate	Lower variation of the pressure centers, better balance.	Sempere-Rubio et al. (42)

FIQ-P, Fibromyalgia Impact Questionnaire Portuguese version; VAS, Visual Analog Scale.

#### 2.6.1. Fibromyalgia impact questionnaire

The translated and validated Portuguese version (FIQ-P) of the Fibromyalgia Impact Questionnaire (36) will be used to access information on the functional capacity and health status of individuals with fibromyalgia. This questionnaire is composed of 20 questions, divided into 10 items that address physical functioning, work status, depression, anxiety, sleep, pain, stiffness, fatigue, and wellbeing.

The item referring to functional ability is the most extensive, which is divided into 11 sub-items, referring to the activities of daily living. The answers are answered on a Likert-type scale from 0 (always able to perform) to 3 (unable to perform). To obtain the results of this item, it is necessary to sum the answers and divide them by the number of valid questions. The next two items refer to the days of the week, being chosen from a number from 1 to 7-questions 12 and 13. For the remaining items 14 to 20, the visual analog scale (VAS)-0 to 10 (maximum value) is used. After obtaining the results, the values vary from 0 to 100, in which the higher the value, the greater the impact of fibromyalgia.

#### 2.6.2. Visual analog scale

For the evaluation of the other symptoms related to fibromyalgia, for the present study, the Visual Analog Scale (VAS) (37) was chosen for the analysis of pain intensity, anxiety level, fatigue level, mood, and quality of sleep. This scale consists of a 100-millimeter horizontal line with boundaries at each end, in which the final rating is measured from the distance from the initial end to the mark by the participant. In this way, each millimeter will be equivalent to one unit. The scoring range will be from 0 to 100, in which the higher the value, the greater the intensity. Scores between 0 and 30 mm will be classified as “mild pain”; between 40 and 70 mm as “moderate pain” and between 80 and 100 mm as “severe pain.”

#### 2.6.3. Fibrodaily

Data regarding pain intensity, anxiety level, fatigue level, mood, and quality of sleep will be continuously collected. A cell phone application will be developed, in which the participants will answer daily the parameters mentioned above. All the outcomes will be defined from VAS with scores from 0 to 10. Zero will constitute the inexistence of pain, anxiety, or fatigue, while intensity will be graded from 1 (mild) to 10 (extremely intense). The outcomes of sleep quality and mood, the scale will be from 0 (bad/not cheerful) to 10 (excellent/extremely excited). To minimize the limitation of poor technology skills, support will be offered to participants. The volunteer will receive a paper spreadsheet to register daily symptoms in case of incompatibility or error during the application's use.

#### 2.6.4. Neuromuscular performance

To assess neuromuscular performance two different tests will be performed. The vertical jump protocol evaluates the neuromuscular performance of the lower limbs, while for the upper limbs, it will be used the Medicine Ball Throw test (38, 39). Before the assessments, a general and specific warm-up of 10 min will be performed (40).

##### 2.6.4.1. Vertical jump

The participants will initially perform vertical jumps, and the heights will be obtained in two different moments: the countermovement jump (CMJ) and the countermovement jump with free arms (CMJFA). Each test will consist of 3 jumps with 2 mins rest between each attempt. The starting position for the CMJ test will be with the hands on the hips and knees fully extended. For the MCJF test, the knees should be extended, but flexion and extension of the upper limbs during the jump will be allowed. During both jumps, volunteers will be instructed to descend to personal counter-movement depth and jump as high and fast as possible. To obtain these data, an optical measurement system consisting of two transmitting and receiving cells (Optojump Next; microgate, Bolzano, Italy) will be used. For performance evaluation and calculation of results, a protocol developed and previously executed will be followed (41).

##### 2.6.4.2. Medicine ball throw

This test aims to evaluate the strength of the upper limbs, more specifically in this case, horizontally. The evaluation will be performed individually with three attempts to throw a 2 kg medicinal ball with 1-min rest between each throw. The other performance criteria will follow a previously published protocol (41). The objective of the test is to quantify the distances obtained from the throw performed by the individual. Measures of reliability (Intraclass Correlation Coefficient and coefficient of variation) will be calculated, in addition to using the mean and maximum value obtained in the trials.

#### 2.6.5. Balance

To assess the balance, a force plate (MuscleLab, Ergotest Innovation, Porsgrunn, Norway) will be used. It will be possible to identify the variation of the pressure centers in the different stimuli or sensorial alterations. A previously used protocol for this evaluation will be used as the basis for the present study (42). The tests will be evaluated following the previously cited protocol: 1. standing position with eyes open (EO); 2. standing position while recalling a stressful day (Dual task [DT]) and standing position with eyes closed (EC).

### 2.7. Intervention

#### 2.7.1. Experimental group

To include participants from all over the country, the training program will be carried out through real-time videos. The protocol consists of 8 weeks of training, consisting of 16 sessions of 50 mins, twice a week on alternate days. To facilitate follow-up during practice and reduce the risk of dropout, the volunteers will be divided into two groups with different times for each intervention. All volunteers will perform the exercise protocol at the meeting via an online (Google Meet platform) and both interventions will be performed during the same shift of the day. Each group will consist of 6 to 8 online participants. The sessions will be conducted and supervised by a physical therapist. Volunteers will be instructed about the exercises, protection and how to use the Borg scale at beginning of the meeting. During the meeting, before each exercise, the movement will first be demonstrated by the physical therapist, and then, sets and repetitions will be informed. To ensure that each participant will do the same number of sets and repetitions, all participants will perform the movement during the professional's count. This format will make it easier to count the rest time.

The program will consist of 10 mins of warm-up, 35 mins of strength exercises, and 5 mins of cool-down. The Borg scale will be used to monitor fatigue and perceived effort during practice (43). The protocol of the exercises to be performed during the training program, as well as their progression, are described in Tables 2, 3, respectively.

**Table 2 T2:** Description of strength training.

**Exercise**	**Name**	**Description**	**Position**	**Muscles**
Exercise 1	Sumô Box Squat	Stand near the chair with your feet wider than shoulder width. Start the movement standing with your hips and sit back. Be careful with the chest, knees, and shins.	Stand	**Primary:** Quadriceps. **Secondary:** Gluteus maximus, medius, and minimus; hamstrings, adductor magnus, longus, and brevis; erector spinae.
Exercise 2	T-exercise	From a standing position, bend at the hips and maintain a neutral spine. Perform dynamic motions by forming a T with the arms and return to starting position.	Stand	**Primary:** Lower and middle trapezius; rotator cuff musculature; posterior deltoid. **Secondary:** Hamstrings; gluteus maximus.
Exercise 3	Torso-elevated push-up	Place your hands on the wall wider than shoulder width with the feet closer together on the ground. Keep the body in a straight line and lower the body until the chest touches the wall. Reverse the movement and raise the body. Be careful with the lumbar spine and elbows.	Stand	**Primary:** Pectoralis major; triceps brachii; anterior deltoid. **Secondary:** Serratus anterior; trapezius; rectus abdominis.
Exercise 4	Bird dog	On quadruped position with the spine in a neutral position, the hands under the shoulders and the knees under the hips. Kick one leg back until the full extension is reached adding an opposite diagonal upper-body movement. Return to starting position.	Quadruped	**Primary:** Gluteus maximus; pectoralis major and anterior deltoid. **Secondary:** Hamstrings; erector spinae; adductor magnus, longus and brevis; gluteus medius, and minimus; multifidus.
Exercise 5	Bridge	In dorsal decubitus keep the knees bent at 90 degrees. Push through the heels and raise the hip. Hold the position in the top for a few seconds and lower the hip to starting position.	*Dorsal Decubitus*.	**Primary:** Gluteus maximus. **Secondary:** Hamstrings; erector spinae; adductor magnus, longus and brevis; gluteus medius and minimus.
Exercise 6	Floor fly	In dorsal decubitus keep the knees bent at 90 degrees. With palms facing, lower the arms in an arching motion. When your elbows hit the floor, back together in an arching motion.	*Dorsal Decubitus*.	**Primary:** Pectoralis major, anterior deltoid. **Secondary:** biceps brachii.
Exercise 7	Single-leg up and down	In dorsal decubitus keep one knee bent with one foot planted on the ground. Keep the opposite hip and knee extended. Up the straight leg until align with the opposite knee. After the movement, return to starting position. Be careful with the lumbar spine.	*Dorsal Decubitus*.	**Primary**: Lower rectus abdominis; psoas major; rectus femoris. **Secondary:** Upper rectus abdominis; internal and oblique.

**Table 3 T3:** Training progression during the program.

**Weeks**	**Sets**	**Repetitions**	**Intensity**	**Rest**	**Perceived effort**
1–2	3	8	Maximal intended velocity^*^	1 min and 30 secs	12–13 RPE
3–4	3	8		1 min and 30 secs	12–13 RPE
5–6	5	6		1 min and 30 secs	14–16 RPE
7–8	5	6		1 min and 30 secs	14–16 RPE

RPE, rate of perceived exertion.

^*^The concentric phase of the movement will be as fast as possible.

The training will include 3–5 sets of 6–8 repetitions depending on the week, as listed in Table 3. The evolution of the training program will be done according to the individuality of each participant. During the protocol, in case of signs of extreme fatigue, reduced range of motion, or inability to perform the movement, an adaptation of the exercise will be made. Table 4 shows the adaptation for each previously defined exercise. Any adjustment will be performed by changing the exercise and/or rest interval. All exercises must be performed with the highest quality, which means technically correct performance and maximum range of motion. Furthermore, the concentric phase should be performed as fast as possible, at the maximal intended velocity.

**Table 4 T4:** Exercise adaptations.

**Exercise**	**Easier adaptation**
Sumô Box Squat	Box squat
T-exercise	Perform extension of the upper limbs with flexion of the elbows
Torso-elevated push-up	Decrease body inclination
Bird dog	Keep the hands on the floor and keep the movement with the legs
Bridge	Decrease the height of the hip lift
Floor fly	Increase elbow flexion during the movement
Single-leg up and down	Decrease the height of the leg lift

